##### Where

In Finland, the open access measurement day will be arranged in a big sports hall and in a few nursing homes. Participants participating in 24-hour measurements will perform their normal daily activities; thus, the location can cover home and various indoor and outdoor environments. In Hungary, the premeasurement day will take place at the Trebag premises and the Rákospalota Elderly Centre. The 8-week training program will take place at protected natural parks in Budapest, which are equipped with various fitness equipment. In Spain, the open access measurement day will be arranged in a public space in the Gernika-Lumo municipality and, possibly, in a nursing home as well. Participants participating in the 96-hour measurements will perform their normal daily activities; thus, the location can cover home and various indoor and outdoor environments.

##### When and How Much

The first measurement events in each country will happen for 1 or 2 days in spring to summer of 2022 at a spacious venue (eg, sports hall, gym, or similar space having enough space to establish the measurement track). Each participant will complete the measurement track once, which will take approximately 20 to 25 minutes in Finland and Spain and 15 to 20 minutes in Hungary. In Finland, the main measurement events will take place first, and smaller measurement events in nursing homes will take place soon after the main measurement session. Participants with armband sensor devices will keep the device for 1 day. In Hungary, after the measurement event, the outdoor fitness training program will start, and it will last for 8 weeks. Participants with armband sensor devices will keep it for 4 days. In Spain, outdoor physical interventions will last for 8 weeks after the measurement event.

##### Tailoring

Participants are expected to participate in all measurement points and preplanned activities; however, they can choose to take part in only a selected number of tests and activities, as participation will be voluntary. The physical fitness testing protocol will be first run in Finland. Modifications will be made to the testing protocol if needs for change are identified based on participant feedback. Thus, it is possible that, in Spain, a slightly modified version of the measurement track will be used. However, for each study participant, the track will be identical.

#### Cross-country Case Study 5: Characterizing the Interaction of the Effects of a Museum Visit on Mobility, Cognition, and Well-being in People With Stroke

##### Why

Although there are studies that have explored the impact of a museum experience on healthy older adults or individuals with acquired and degenerative neurological conditions [29-31], there is a lack of studies investigating the interaction of the effects of a museum visit on mobility, cognition, and the lived experience of individuals with stroke, as well as on older healthy aging adults using advanced technologies that measure mobility, cognition, well-being, and UX. To this end, this small-scale pilot aims to obtain measurements of mobility, cognition, and well-being of people with stroke and healthy aging individuals using innovative technologies to explore the lived experiences of these individuals as they participate in a museum environment. The collected data will be used to (1) study the feasibility of conducting a series of diverse measurements in a museum setting, (2) study the acceptability of such interventions in a museum setting, and (3) create a user model that can be adopted to describe people with disabilities visiting a museum in future big data collection.

##### To Whom (Sample Size and Recruitment)

In Canada, a total of 30 persons will be recruited via a patient contact list from a rehabilitation hospital and the Association Québécoise Des Personnes Aphasiques. In Greece, a total of 20 persons will be recruited via collaboration with the B Department of Neurology, AHEPA University Hospital. All participants will be aged between 55 and 85 years, have normal or corrected vision and hearing, and walk independently with or without technical aids. Group A will comprise 15 persons with stroke, including 6 with mild or mild to moderate aphasia in Canada and 10 people with stroke, including 4 with mild or mild to moderate aphasia in Greece. Group B will comprise 15 healthy controls for Canada and 10 healthy controls for Greece. For both groups, the key exclusion criteria will include (1) postural and balance disorders, (2) severe psychiatric disorders (excluding depression or anxiety), (3) recent history of alcohol or substance abuse, (4) general anesthesia within the past 6 months, (5) pain >2 on the visual analog scale, and (6) >10 on the GDS. In group A, participants with severe or global aphasia or scoring <20 in a mini mental state examination (MMSE) will be excluded. In group B, participants having a <26 score in MMSE will be excluded.

##### What (Materials)

The physical spaces of the museums (benches, stairs, exhibition halls, and vestibules), works of art (paintings and sculptures, casts, and antiquities), and audio guides will be used in the study. Furthermore, the following technologies will be used both in Greece and in Canada to monitor the participants before, during, and after their visit: (1) Pupil Labs eye-tracking glasses and (2) smartwatch (eg, Apple Watch or Fitbit 4). In Canada, additional materials will be used for monitoring, namely the (1) near-infrared spectroscopy (NIRS) system, (2) pressure sensitive walkway (Gaitrite), (3) portable force platform to measure body weight distribution and center of pressure oscillations, and (4) APDM inertial sensors placed in the participants’ thorax and tibia. Physical standardized test alternatives will be used in Greece to gather similar information. Specifically, the physical test battery will include (1) 10 m walk test, (2) Tinetti test, (3) Berg Balance Scale, (4) 30-inch chair stand test, (5) Timed Up and Go test, (6) 2-minute walk test, and (7) balance on 1 leg test. The following test batteries will be used for previsit profiling: (1) for cognitive status measurement, the MMSE or Montreal Cognitive Assessment, and (2) GDS. A neuropsychological evaluation will also be conducted before each session, specifically the (1), Rey Auditory Verbal Learning Test, Stroop Test, and Trail Making Test A+B; (2) Warwick–Edinburgh Mental Well-being Scale; (3) State-Trait Anxiety Inventory and visual analog stress; (4) Visual Analog Pain Scale; (5) Multidimensional Fatigue Inventory; (6) EuroQol-5 dimensions; and (7) Environment Quality and Satisfaction Tool.

##### What (Procedures)

The study will run in 2 sessions (session 1 and session 2), and session 1 will comprise 2 options based on the participants’ profiles. The procedures that will be followed in each session are described below.

In session 1 (option A; participants with stroke and aphasia and half of the control participants), after signing the consent form, participants will be asked to wear the tracking and monitoring equipment (smartwatch, eye-tracking glasses, and headphones for audio guide). For each of the 3 chosen works of art, the participants will listen to the description of the work of art (audio version of the written information that accompanies the work), then listen to the adapted description, and answer some questions posed by the on-site assistant who will assess their experience.

For session 1, option B (participants with stroke and no aphasia and half of the control participants), after signing the consent form, participants will be asked to wear the tracking and monitoring equipment (smartwatch and NIRS cap only for Canadian participants). The participants of this group will be asked to walk twice through a predetermined circuit of 6 different works of art (painting or antiquities) and complete a guided tour. In each painting, participants will be instructed to (1) analyze each painting by focusing on the message or intention communicated by the artist, the symbolic meaning, and the composition of the artwork (ie, analytical condition); and (2) view the painting without analysis (ie, control condition).

In session 2 (all participants), participants will be asked to wear the tracking and monitoring equipment (smartwatch) and walk at their own pace on the predetermined tour of the spaces and the built environment of the museum (stairs, elevator, bench, chair, and toilet). Breaks will be provided as needed and requested by participants.

In both data collection sessions, the lived experience of individuals, as well as their opinions regarding the evaluations at the museum, will also be documented to understand the lived experience of all individuals involved.

##### Who Provided

Researchers from the study, as well as trained research assistants or students, will be present for each session at the museum and will be responsible for the placement of the various forms of technology on the participants and for all data collection.

##### How

All sessions will be held face to face, and only 1 participant will be tested at a time. After signing the consent form and completing the previsit testing batteries with a research assistant in a reception room, the participant and their caregiver or companion will go to the museum exhibit hall. Before the museum experience, participants will be equipped with the following devices: in session 1 option A, (1) smartwatch (Apple Watch or Fitbit), (2) headphones for the audio guide, and (3) eye-tracking glasses; in session 1 option B, (1) the NIRS cap for Canadian participants and (2) a smartwatch (Apple Watch or Fitbit); and in session 2, a smartwatch. In each session after the museum visit and the performed activities, the devices will be removed, and participants will return to the reception room, where a brief questionnaire Will be administered. The participants will receive a smartwatch that they will keep until they return in the following week for session 2.

##### Where

All testing in Canada will be performed at the Montreal Museum of Fine Art, Pavilion for Peace. In Greece, testing will be conducted at the Museum of Casts and Antiquities, School of Philosophy of the Aristotle University of Thessaloniki, Greece.

##### When and How Much

The measurement events in each country will happen for 1 or 2 days in spring to summer of 2022, with a 1-week period between sessions. Session 1 will last a total of approximately 1.5 hours, and session 2 will last approximately a total of 1 hour.

### Analysis

#### During Phases 1 and 3

Inductive qualitative content analysis will be conducted to answer RQ1 to RQ3. First, an iterative open coding process will be conducted, and preliminary categorization will be generated to classify the raw data received from the Microsoft Excel file templates, interviews, workshops, and Mentimeter brainstorming. Next, the data will be grouped by reducing the number of categories by grouping similar technologies, methods, tools, and validated scientific questionnaires to identify alternative approaches to execute a certain research task. Finally, abstraction will be conducted to define the main categories and create possible subcategories under each main category. The popularity of the different technologies, methods, tools, and validated scientific questionnaires among VITALISE Living Labs will be identified by calculating frequencies and percentages. To evaluate the acceptance and consensus of the defined harmonized research protocols among VITALISE Living Labs and external harmonization bodies, an iterative web-based Delphi process will be conducted until a supermajority agreement is reached (ie, at least a 70% acceptance rate) [32].

#### Data Analysis Plans for Case Studies During Phase 2

The *main quantitative analysis approaches* will include descriptive data (eg, mean, frequency, and SD) to characterize the participants’ (sociodemographic variables) and summarize the results of the questionnaires. Chi-square tests will be used to detect the associations between the categorical variables when needed. To explore whether the outcomes of the interventions are significant, parametric (eg, paired and unpaired 2-tailed *t* tests, Pearson correlation, and 1-way analysis of variance) and nonparametric tests (Wilcoxon signed-rank test, Mann–Whitney *U* test, Spearman correlation, and Kruskal–Wallis test) will be conducted to investigate the possible research findings and future research directions. Case studies evaluating the impact of the intervention will include 2 temporal data collection moments, 1 before and 1 after the intervention period, to validate the changes that might occur. Standardized statistical tools will be used for data analysis, such as SPSS (IBM Corp) and Microsoft Excel. Sensor data analysis will be used by the sensor device–related software features, for example, for eye-tracking data or wearable sensor temporal activity data analysis, when case studies use them for data collection. The main quantitative analysis approaches include the inductive qualitative content analysis executed in phases 1 and 3. For case study 5, hermeneutic analysis of the phenomenon and content analysis of the photos will also be performed. For all cases, answers to the questionnaires will be extracted and triangulated with quantitative data.

### Incentives

The VITALISE project consortium Living Labs will receive EU funding (under grant agreement 101007990; April 2021 to March 2024) for conducting the proposed study. According to the consortium agreement, each Living Lab is obligated to conduct such a study; therefore, funding is tightly interlinked with the delivery of the proposed study. Users’ (ie, study participants) intrinsic and extrinsic motivations are key drivers of Living Lab research [33]. Prior studies have identified the following motivational factors that also create the foundation for the case study incentives [34]: (1) projects improving own health or are close to participants’ health needs or interests; (2) projects helping the wider community and contributing to the common good; (3) contributions to formal acknowledgment instead of financial compensation or recognition by others; (4) knowledge seeking, curiosity, and being entertained; (5) desire to feel competent and self-determined; and (5) the possibility to test new innovative products and services. In addition to the abovementioned motivational factor–driven incentives, the following case study incentives will be provided:

Case study 1: Free of charge digital coaching mobile app training program for 8 weeks focusing on improving well-being and social participation in general and how to deal with challenges related to retirement; The monetary fees offered to compensate for the participation costs (eg, traveling) are €20 (US $20.90) to €40 (US $41.80) euros for Austrian participants and €15 (US $15.70) to €20 (US $20.90) for Belgium participants, and internet-connection will be reimbursed on request of participantsCase study 2: Free of charge measurement of personal physical fitness level and cognitive capabilityCase study 3: Free of charge use of new services aimed at improving physical, psychological, and emotional health in 2 weekly 30-minute sessions for 8 weeksCase study 4: Free of charge measurement of personal physical fitness level, including the ability to compare own results with the peer group; for Spain and Hungarian participants, free of charge training program for 8 weeks focusing on improving physical fitnessCase study 5: 2 museum tickets

### Data Management and Ethics Statement

The VITALISE project will encapsulate multimodal data collection phases toward the development and evaluation of novel supportive interventions related to everyday living environments. As the individuals who will provide the data are the cornerstone of these data collection phases, special attention will be given to the compliance of the collection processes with ethical regulations and guidelines on research involving human beings, as well as on the safety of the sensors, tools, and devices involved, and the protection of personal and health data. Project deliverable *D1.2 First version of ethics and safety manual* constitutes a reference guide for the VITALISE investigators by reporting on the international, European, and national ethical regulations, device safety standards, and certifications. Deliverables will also include ethics management and data control actions and guidelines adopted by the consortium that will assist and monitor its compliance with the medical research regulations and guidelines. In addition, a thorough consent form template will be included and will be used by all partners according to their specific protocols.

Deliverable D1.2 presents the first plan for the VITALISE project scheduled data collection to be compliant with the reported regulations and guidelines and evaluates potential concerns early to be mitigated effectively through the proper management of ethical and data handling–related issues within each country and between different countries. The D1.2 deliverable will be publicly available after the completion of the European Commission review process (expected publication time will be by the end of 2021). It is highlighted that D1.2 is a living document that will be regularly updated throughout the project, leading to its final version (Deliverable 1.3) on project month 24.

## Results

As of September 30, 2021, project deliverables *D1.2 First version of ethics and safety manual* and *D2.1 Standard Version 1*, presenting the state of the art for the Living Lab services, methods, and tools, have been submitted for the European Commission review process. Both deliverables will be publicly available after completion of the European Commission review process (expected publication time will be by the end of 2021). Both deliverables are living documents that are regularly updated throughout the project, leading to its final version by month 24. At the time of submission, the status of the VITALISE project is active, and materials for national ethics boards are being prepared. After receiving acceptance from ethics boards, participant recruitment for case studies will be started latest by June 2022. The study will be finished by March 2024.

## Discussion

### Harmonization Process Outcomes

The outcomes of this study enable Living Labs to exploit similar research protocols, devices, hardware, and software for interventions and complex data collection purposes when developing big data–driven hybrid personas. The harmonized protocols will speed up and improve the research quality and offer novel possibilities for open data sharing, multidisciplinary research, and comparative studies beyond current practices. Researchers will have wider, simplified, and more efficient access and services to Living Lab RIs, irrespective of location. This enables researchers to focus on the research itself instead of managing practical challenges. Economies of scale and improved use of resources across Living Labs have also been realized because of the less duplication of services and common development and optimization of operations.

### Case Study Outcomes

#### Case Study 1

This study will allow a better understanding of how digital coaching can influence individuals’ well-being and social participation by motivating older adults to practice a healthy lifestyle. Monitoring the effects of AIT’s digital coaching app use may shed light on the capability of a digital coach for helping retirees maintain (and improve) social relationships and activities that could be put at risk by their withdrawal from the workplace. In addition, the results will also allow the optimization of the UX of deployed coaching mobile apps. By setting up this case study at 2 different sites, Belgium and Austria, specific results related to these different social and cultural contexts are also expected.

#### Case Study 2

The results of the randomized controlled trial will show that it is feasible to conduct a randomized controlled trial of yoga in a virtual and sensor-assisted Living Lab environment using the described protocol. Moreover, the collection of novel sensor data from the experiment is expected to provide insightful information about the physical and psychological status of the participants.

#### Case Study 3

The results of this study will allow the analysis of effectiveness, usability, and acceptance of the described Gradior Active intervention. It will state the pillars for evidence-based decision-making on investment in the upgrade and modernization of the prototype; at the same time, it will ensure a final co-design sprint with participants to orient the incremental development plans.

#### Case Study 4

The main results will focus on understanding older adults’ physical fitness levels by defining and testing comprehensive testing patterns in a cross-country setting. Single test results with reference values exist; however, surprisingly, a wider understanding of older adults’ fitness levels is lacking. From prior studies, it is acknowledged that the vast majority of the participants recruited via open calls will be persons with good fitness and functioning levels. Therefore, older adults with lower physical fitness will be recruited from nursing homes to also cover more fragile and less fit older adults. By combining the daily physical activity level sensor measures and physical fitness test results, novel and insightful information about the physical status of the participant can be verified. The perceived UX of the proposed comprehensive physical fitness level research protocol will be compared with a well-established but less comprehensive protocol. It is expected that there will be no significant differences regarding UX; therefore, in the future, a more comprehensive protocol should be applied to reveal a better understanding of the older adults’ physical fitness levels. Furthermore, the pre- and posttraining period physical fitness levels will be compared in the cases of the Spain and Hungary case studies. These results are expected to reveal that the training program affects participants’ physical fitness level as well as provide suggestions from participants on how to improve the training program.

#### Case Study 5

Although this study is exploratory, it is anticipated that museum visits will be associated with (pre and post) changes in mobility (endurance, navigation, posture, and balance) and cognition (attentional control and auditory comprehension in dual tasking) and will generate a well-being effect (positive experiential experience and decrease in anxiety state). Moreover, considering that museums or any public places solicit locomotor capacities (endurance, navigation, posture, and balance), it is expected that the visit will be associated with a greater variation in motor skill, cognition, and well-being in all our most vulnerable groups (stroke) compared with the control group. Finally, the environmental conditions and characteristics that do or do not influence the above variables will be identified. The latter may result in modifications that will favor inclusion and ultimate participation of aging individuals, especially those living with stroke and language limitations.

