##### To Whom (Sample Size and Recruitment)

In Finland, the sample group will comprise older adults aged >67 years. To recruit older adults with varying physical fitness levels, the following strategy will be applied: open calls to promote free of charge physical fitness level measurement as part of a research project will be published in local newspapers and social media channels in collaboration with the local city administration responsible for older adult services. Furthermore, the collaboration will be conducted with selected nursing home administrators to recruit participants with weaker physical fitness levels directly from nursing homes. It is estimated that approximately 200 to 400 persons will be recruited via open calls and approximately 50 persons from nursing homes. In Hungary, the sample group will comprise people aged >55 years. Social media, posters in outdoor trails and fitness parks, former contact lists, and snowball sampling will be used to recruit the participants. It is estimated that 30 to 50 persons will be recruited; however, because of dropouts during the training program, only 20 are expected to take part in the posttest. In Spain, the main target sample will be men and women aged between 60 and 80 years. of Participants will be recruited in collaboration with the city council of Gernika-Lumo, local nursing homes, and retiree associations. It is estimated that 20 to 40 people will be recruited from all collaborative organizations.

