##### What (Procedures)

The following physical fitness components will be covered in the physical fitness test in Finland and Spain: cardiorespiratory endurance, muscle strength and endurance, balance, agility, speed, flexibility, and body composition. After signing the consent form and filling the quality of life questionnaire (World Health Organization Quality-of-Life Scale), the participants will go through the following measurement points step by step in selected locations (ie, sports halls, nursing homes, fitness parks, and outdoor facilities): (1) 6-minute walk test or nonexercise cardiorespiratory fitness test, (2) handgrip strength test, (3) 30-second arm curl test, (4) 30-second chair stand test, (5) Smartifier balance board test, (6) 8-foot up-and-go test, (7) backward walk test, (8) 10 m walk test, (9) chair sit-and-reach test, (10) back scratch test, (11) height and body composition measurements, and (12) peak expiratory flow measurement. In Hungary, which is used as a control group, physical fitness will be measured by following a protocol defined in the senior fitness test manual [28]. After finishing the measurement track, participants will fill the UEQ, which also includes an open text box to propose improvement suggestions or give complaints about the testing procedure.

In Hungary and Spain, the physical fitness testing battery will be used to determine the baseline (T0, before the start of the training program intervention) and conduct the postmeasure (T1) at the end of the 8-week training program. Participants’ daily activities will also be measured with the armband device for 4 days during the training period. In addition, in Spain, some of the participants will also use a smart wristband watch (Galaxy Watch 3). In Hungary, the training program will include outdoor training on fitness trails with 19 stations in a 1.5 km route. Feedback will be collected from participants after the training intervention. In Spain, outdoor training on recreational football will be performed in a network of distributed resources and public spaces. Feedback will be collected from participants after the training intervention.

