##### How

During the measurement day in Finland and Spain, there will be an open access period when measurements will be conducted by following the walk-in principle. Participants will circulate individually from the measurement point to another, where they will receive instructions from students (physiotherapy or similar). After finishing the measurement track, participants will go to the meeting point where general reference values and the interpretation of the results can be self-read from the presented materials. At the meeting point, participants will also fill the UEQ questionnaire. In Hungary, the process will be similar; however, participants will be invited, and the measurement track will be based on a protocol defined in the senior fitness test manual [28].

The physical fitness testing protocol will be first run in Finland. Following this, modifications will be made to the testing protocol if needs for change are identified based on participant feedback. The same or revised protocol will then be used in Spain to collect cross-country data. In Hungary, a different protocol [28] will be used to get the baseline for UX and be able to compare how the extended measurement protocol influences the UX. At the end of the project, result comparisons regarding measurement day experiences will be made between the 3 countries and 2 different measurement protocols.

The participants receiving the armband device will be invited to a specific location (eg, university campus), where they will receive detailed information about the test and how to keep the activity diary. In Spain, some of the participants will also receive a Galaxy Watch 3 device, which is used for similar purposes as the armband device. In Finland, participants will keep the device for 1 day (24 hours). In Hungary and Spain, participants will keep it for 4 days (96 hours). Owing to the limited number of devices and device rotation, the measurement time will vary between participants.

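### Case study 4 draws a recommendation for the longer fitness protocol from an expected non-significant UX difference, which would not show similar UX, in a contrast where protocol cannot be separated from country

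*Protocol article*

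**What the plan says.** The Discussion (Case Study Outcomes, Case Study 4) says that perceived UX of the comprehensive protocol "will be compared with a well-established but less comprehensive protocol". It then continues: "It is expected that there will be no significant differences regarding UX; therefore, in the future, a more comprehensive protocol should be applied". The reason given for wanting the longer protocol is that it tells more about older adults' fitness.

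The comparator is described in two places. Case Study 4, How: "In Hungary, a different protocol [28] will be used to get the baseline for UX", with the stated purpose of seeing how the extended protocol influences UX. Case Study 4, What (Procedures): "In Hungary, which is used as a control group, physical fitness will be measured by following a protocol defined in the senior fitness test manual". Finland and Spain use the long track.

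The groups are recruited differently. "In Finland, the sample group will comprise older adults aged >67 years", while "In Hungary, the sample group will comprise people aged >55 years", and Spain targets ages 60 to 80. Finland and Spain admit participants on a walk-in basis. "In Hungary, the process will be similar; however, participants will be invited".

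The section Data Analysis Plans for Case Studies During Phase 2 lists t tests, analysis of variance, Mann–Whitney, Kruskal–Wallis, chi-square and correlations. For comparing groups, all of these are tests of difference.

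**The concern.** Two things are wrong with the step from the expected result to the recommendation.

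First, a test of difference that fails to reach significance is compatible with equal UX, and equally with a real loss that the sample was too small to detect. Reading it as evidence of no loss rewards imprecision: the fewer Hungarian participants there are, the more easily the expected result is obtained.

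Second, the article wants to learn what the extended protocol does to UX, but the shorter protocol exists in one country only. A Hungarian difference in rating habits, in the staff running the stations, or between invited and walk-in participants would appear as a protocol effect, or would hide one.

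At stake is the article's statement that the longer protocol should be used in future. It could be made although UX is moderately worse, or withheld because of a country difference unrelated to the protocol.

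**Working it through.** The article gives no power calculation, margin, significance level or SD for the UX comparison, so there is no stated figure to reproduce. What follows is an illustration from its sample sizes.

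**Inputs from Case Study 4, To Whom**
- Hungary: 30 to 50 recruited. The 20 expected at post-test are not used, because the comparison concerns the measurement-day experience.
- Finland: 200 to 400 by open call, plus about 50 from nursing homes.
- Spain: 20 to 40.
- Long track pooled: 200 + 50 + 20 = 270, up to 400 + 50 + 40 = 490.

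**Assumptions (not in the article)**
- Two-sided 5% level, equal SDs, differences in SD units, normal approximation.
- Finland and Spain pooled.

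**Formulas**
- SE = √(1/n₁ + 1/n₂)
- 95% CI half-width = 1.96 × SE
- Probability that a true deficit d is non-significant ≈ Φ(1.96 − d/SE)

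**Hungary 30 versus 270.** SE = √(0.0333 + 0.0037) = 0.192; half-width 0.38 SD.
- d = 0.3: Φ(1.96 − 1.56) = 66%
- d = 0.5: Φ(1.96 − 2.60) = 26%

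**Hungary 50 versus 490.** SE = √(0.0200 + 0.0020) = 0.148; half-width 0.29 SD.
- d = 0.3: Φ(1.96 − 2.02) = 48%
- d = 0.5: Φ(1.96 − 3.37) = 8%

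**Effect of a smaller comparator.** With the long-track group held at 270, a 0.3 SD deficit is missed 50% of the time with 50 Hungarians (SE 0.154) and 66% with 30.

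**Spain alone versus Hungary, d = 0.5.**
- 20 versus 30: SE 0.289, missed 59%
- 40 versus 50: SE 0.212, missed 35%

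**What can and cannot be separated from protocol**

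| Factor | Short protocol (Hungary) | Long protocol (Finland, Spain) | Separable? |
|---|---|---|---|
| Country | Hungary | Finland, Spain | No |
| Staff | Local staff with a qualified leader | Supervised physiotherapy students; local staff with sports-science students | No |
| Entry | Invited | Walk-in | No |
| Age | Over 55 | Over 67; 60 to 80 | Yes, ranges overlap |
| Finnish nursing-home group | – | About 50, recruited separately | Yes, by separate analysis |

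Setting the nursing-home group aside costs almost no precision, because the Hungarian sample dominates the SE. Hungary against Finnish open-call participants only:
- 30 versus 200: 1.96 × √(1/30 + 1/200) = 0.38 SD
- 50 versus 400: 1.96 × √(1/50 + 1/400) = 0.29 SD

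**The case against.** The sentence is a Discussion expectation in a condensed article, about a comparison secondary to the fitness results. A reader might infer that it is a formal adoption rule, or that the UEQ p-value decides which protocol is harmonised. The documents support neither. The sentence names no test or threshold, and harmonisation of the project's research protocols is settled by workshops and repeated voting to at least 70% acceptance (When and How Much; Analysis, During Phases 1 and 3). Acceptability is also probed by an open text box on the UEQ, and the track may be revised on participant feedback before it is used in Spain. All of this stands and lowers the weight of the point.

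A reader might also infer that the plan could easily endorse a clearly less acceptable protocol. The pooled figures do not bear that out at 0.5 SD, where only 8% to 26% of true deficits would be missed. The risk lies mainly with smaller deficits, or if Spain alone is compared with Hungary.

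Nor is every group difference inseparable from protocol: age and the Finnish nursing-home group can be handled in analysis.

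Finally, the absence of a margin is not itself a fault, since a fuller case-study protocol or analysis plan may hold one. But a margin elsewhere would not repair a printed conclusion drawn from non-significance, and no analysis plan can undo the allocation of the short protocol to one country.

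**Conclusion.** The point holds in limited form and should be fixed. The stated inference is invalid: the recommendation follows from an expected non-significant difference, and that result would not show similar UX. At the planned sizes a 0.3 SD deficit would be missed 48% to 66% of the time and a 0.5 SD deficit 8% to 26%, with a 95% confidence interval half-width of 0.29 to 0.38 SD. These figures rest on an assumed 5% two-sided level, equal SDs and pooling of Finland with Spain; the article does not say what UX difference would matter. The logical fault does not depend on them.

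Separately, the contrast cannot isolate the effect of the protocol from country, staff and entry mode, whatever the sample size. Hungary can serve as a descriptive reference for UX, but not as a control that identifies the protocol effect.

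**What to change.** **Wording and analysis changes**
1. In Discussion, Case Study 4, remove the *therefore* that bases the recommendation on non-significance.
2. Report the UEQ difference (long minus short) with its 95% confidence interval. Support the longer protocol on UX grounds only if the lower limit lies above minus a margin fixed before the Finnish event, which runs first. Otherwise state that the result is inconclusive.
3. Adjust for age, and analyse Finnish open-call participants separately from nursing-home participants.
4. Label the cross-country contrast descriptive, and say that country and protocol are confounded. If the track is revised after Finland, show Spain separately.

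**Cost.** No new data are needed. The price is a less comfortable conclusion. For one-sided 2.5%, 80% power, no true difference and about 9:1 allocation, the Hungarian sample needed is (1.96 + 0.84)² × (1 + 1/9) / margin². That gives about 35 for a 0.5 SD margin and about 97 for 0.3 SD. At 30 to 50 Hungarians, power is 74% to 92% for a 0.5 SD margin but 34% to 52% for 0.3 SD, so a narrow margin will often give an inconclusive result. These margins are illustrations; the study team must choose one.

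**Optional, not required.** Randomly allocating some Finnish open-call arrivals, say 1 in 5, to the short track would remove the country confounding. It gives 40 versus 160 up to 80 versus 320, with half-widths of 0.35 to 0.25 SD. This is a design change. It needs a second track at a walk-in event and gives 40 to 80 people fewer measurements, when free measurement is their incentive. Power at a 0.3 SD margin would still be only about 40% to 67%.
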